# STUDY DESIGN

For this study, an individually randomised, 3 arm, parallel group design will be employed.

Due to the nature of the intervention, it will not be possible to blind participants, clinicians or some of the study team to the treatment allocation once the intervention commences, but they will be blind at the point of randomisation.

Patients’ participation in the study will last 3 months from randomisation to final follow-up. Details of the sequence and duration of all study periods are included in the appendix together with the flowchart of the project.

Briefly, participating practices will search their records for eligible participants who meet the essential inclusion criteria: a) adults and b) with a record of high LDL cholesterol over the last 24 months. Invitation letters will be sent with the team contact information and study details, including other inclusion criteria a) participant is primarily responsible for the household grocery shopping and b) participant shops at Tesco at least once a week using a Tesco storecard.

Interested participants who believe they meet the criteria will be invited to contact the central research team via email who will assess them further over the phone to check eligibility. Those who meet all the eligibility criteria will be booked for the first baseline visit. Previous to the first baseline visit, participants will be asked to provide the first 24h dietary recall (using a validated online questionnaire performed on a computer). This data will be stored independently of the study team before full consent is obtained.

At the baseline visit participants will provide full informed consent and a blood sample by fingerprick will be taken by the central research team. Additionally, the central research team will collect other baseline measures, including a second 24h dietary recall, weight and height, blood pressure and their Tesco’s clubcard number. Once the blood tests confirm that each participant has raised LDL cholesterol and that they have completed two dietary recalls, the central research team will randomise them to one of the three interventions. Those allocated to brief advice session or brief advice session with purchasing report will be booked for an appointment with the health professional at their practice within a week after the baseline visit preferably. Those allocated to the control arm will receive usual care, which consists of providing their blood results.

All participants will come back after 3 months for a third visit (follow up) in which some outcome measures collected at baseline will be repeated, including the blood sample, the 24h dietary recalls, weight, blood pressure, and a questionnaire to assess acceptability of the intervention. Additionally, at the end of the study period, all participants will receive a purchasing report regardless of their treatment group allocation as well as the results of their final blood test.

# PARTICIPANT IDENTIFICATION

## Study Participants

The study population will include 112 adults ≥18 years of age with confirmed high LDL cholesterol (>3 mmol/L) at baseline, who will be recruited and randomised to intervention or comparator groups.

Screening and recruitment will be performed locally through primary care practices to identify eligible individuals. Screening criteria will be: age ≥18 years with a blood test in the GP records which indicate LDL-cholesterol >3.5 mmol/L (or total cholesterol >5.5 mmol/L if an LDL measure is not available) in the past 24 months, who will likely benefit from a lower SFA diet with no pre-existing conditions that warrant exclusion.

Participating practices will search their records to find people who meet the screening criteria and will send invitation letters explaining the benefits of joining the study and the contact information to take part in the study. Patients whose GP judges not able to meet the demands of the study or unlikely to adhere to study procedures as stated in the protocol will not be invited to take part in the study. All eligible participants will have to have a blood test to confirm that they have high LDL at the moment of recruitment to be eligible for the study.

## Inclusion Criteria

- Male or Female, aged 18 years or above.
- Express a desire for support to improve the nutritional quality of their diet to reduce their CVD risk.
- Primarily responsible for household shopping (e.g. complete at least half of their household shopping).
- Shops mainly at Tesco (e.g. at least once/week instore and/or online) using a Tesco’s storecard.
- Have had a Tesco’s storecard registered exclusively under their name for at least 3 months before recruitment.
- Computer literate (e.g. use email regularly and is able to perform dietary questionnaires online).
- Participant is willing and able to give informed consent for participation in the study.
- With confirmed LDL cholesterol above 3 mmol/L at recruitment.

## Exclusion Criteria

- Unable to read and understand the instructions provided in English.
- Pregnant, or planning to become pregnant during the course of the study.
- Started cholesterol-lowering medication in the last 3 months.
- Planned changes to cholesterol-lowering medication in the next 3 months.
- Existing cardiovascular conditions: heart attack or stroke or new diagnosis of atrial fibrillation within the last 3 months; heart failure of grade II New York Heart Association and more severe, or prolonged QT syndrome, angina, Arrhythmia, or familial hyperlipidaemia.
- Currently or recently (within the last 3 months) participating in another intervention study which likely affects the outcomes measured in this study.
- Patients that the GP judges not able to meet the demands of the study or unlikely to adhere to study procedures as stated in the protocol.

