## Eligibility Assessment

Participants who are interested in taking part will contact the central research team on the email provided to them in their letter from the GP. The central research team will discuss study participation with potential participants (by telephone) and undertake eligibility assessment. If the potential participant appears eligible and would like to attend a baseline assessment to confirm eligibility, they will be offered an appointment at their GP practice.

The central research team will post a Participant Information Sheet (PIS) and confirmation letter. Participants will be asked to complete the first 24h dietary recall before the first baseline visit. This data will be stored independently of the study team before full consent is obtained. Participants will be also informed that any data provided before the baseline visit will be destroyed if they decide not to continue taking part in the study, are found to be ineligible or they don’t attend the baseline visit.

When the participant attends the practice, the central research team will provide information as described in the PIS to seek informed consent and will check eligibility for inclusion in the study by assessing the inclusion and exclusion criteria as described above; and confirming elevated LDL cholesterol with the blood sample taken at this baseline visit.

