## Three-month follow up assessment

A follow up and final visit will be completed at least 3 months and no more than 4 months after randomisation to assess the main study outcomes. Therefore, all the measures collected as part of the baseline visit will be repeated following the same procedures and conditions as described above.

The central research team will collect the following measurements at the practice:

- Fasting fingerprick blood sample, to be analysed for blood lipids (LDL, HDL, total cholesterol, non-HDL cholesterol, total cholesterol/HDL ratio and triglycerides) using a portable lipid testing system, will be taken by the central research team,
- Any changes in knowledge with regards to diet and SFA as well as intervention acceptability collected by questionnaire,
- Changes to relevant medical history and all concomitant medication,
- Dietary intake will be collected using a validated web-based 24-h recall dietary questionnaire, which will be completed twice at follow up, once prior to the follow up visit, and a second one at the in-person visit. Participants will be given the opportunity to come to the practice to complete their dietary recall if they are unable to access a computer and internet at home,
- Seated systolic and diastolic blood pressure,
- Weight.

- Changes to drug treatments during the course of the study: the clinical team in the practice will decide which, if any medications need to be adjusted as a result of changes in health status during the course of the study. However, we will ask participants and clinicians to refrain from altering any lipid-lowering medication during the 3-months of follow-up unless strictly necessary.

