## The Number of Participants

The total number of participants we intend to recruit for this study is 112, with a sampling ratio of 1:3:3. Therefore, 16 participants will be allocated to control, and 48 participants will be allocated to each of the two active interventions.

Previous studies such as highly controlled interventions in populations with high CVD risk have achieved absolute changes in %SFA intakes of around 4-5%^6 7^, and a short-term change in LDL-cholesterol of 0.32 mmol/L by a low-intensity primary care-based intervention^10^. Attrition rates have been reported to be quite low in short term primary care-based trials^10 20^, so we could assume around 10% attrition rate in our study. In order to detect a reduction of 3% in %SFA intake (3% standard deviation) between each intervention and control with 90% power and two-sided α=0.05 using intention-to-treat analyses, we will need 16 participants in the control group and 48 in each intervention arm to account for 10% attrition and multiple comparisons. By recruiting 48 participants in each active intervention arms, we will be able to detect a further difference between these two arms of 2% (3% SD) with 90% power.

In addition, this sample size will allow to detect a change in LDL cholesterol of 0.3 mmol/L (SD 0.8) between each intervention and control with 60% power using a 2-sided α=0.05.

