## Approvals

The protocol, informed consent form, participant information sheet and any other relevant intervention materials will be submitted to an appropriate Research Ethics Committee (REC), and host institution(s) for written approval.

The Chief Investigator will submit and, where necessary, obtain approval from the above parties for all substantial amendments to the original approved documents.

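### The exclusion for planned cholesterol-lowering medication changes ends at 3 months, but the final lipid sample can be taken up to 4 months after randomisation

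*Protocol*

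**What the plan says.** Three parts of the protocol bear on lipid-lowering medication around the final sample.

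- **Entry.** Section 7.3 (Exclusion Criteria) excludes people with "Planned changes to cholesterol-lowering medication in the next 3 months". Under Eligibility Assessment (section 8), the research team at the baseline visit "will check eligibility for inclusion in the study by assessing the inclusion and exclusion criteria as described above". Appendix B lists randomisation under that same first baseline visit.
- **Final visit.** Section 8.5.1 sets the visit "at least 3 months and no more than 4 months after randomisation" and includes a fasting fingerprick lipid sample. Medication changes are recorded there.
- **During follow-up.** Section 8.5.1 also says participants and clinicians will be asked to "refrain from altering any lipid-lowering medication during the 3-months of follow-up unless strictly necessary".

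Two other statements help in reading these. Section 6 says that "participation in the study will last 3 months from randomisation to final follow-up". Another exclusion in the section 7.3 list is tied to the study itself rather than to a number of months: "Pregnant, or planning to become pregnant during the course of the study".

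**The concern.** An exclusion for planned medication changes is there to keep foreseeable drug effects out of the outcome lipid measurement. For that it has to reach the date of the measurement. Here it stops at the earliest date on which the sample may be taken, so someone who already plans to start or change a cholesterol-lowering drug in month 3 to 4 passes the criterion and may make the change before the sample.

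Such a plan is plausible in this population. Section 4 describes people with raised LDL who may be joining to avoid long-term medication, and trying diet for three months before starting a drug would fit that. This is an inference; the protocol gives no rate.

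Only the lipid outcomes are at stake. They are secondary, and section 11.2 gives limited power for LDL: "a change in LDL cholesterol of 0.3 mmol/L (SD 0.8) between each intervention and control with 60% power". The control arm has only 16 participants, so a single drug-affected value has some weight there.

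**Working it through.** **Inputs**

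- Look-ahead of the exclusion: 3 months from the eligibility check (section 7.3).
- Eligibility check and randomisation: both at baseline visit 1 (Eligibility Assessment; Appendix B). I take the lag between them as zero. If the answer given at the earlier telephone screen were relied on instead, the gap would grow by that interval, which the protocol does not state.
- Permitted sample date: 3 to 4 months after randomisation (section 8.5.1).

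**Size of the gap**

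- Smallest: 3 − 3 = 0 months, for a visit exactly at month 3.
- Largest: 4 − 3 = 1 month = 365.25 / 12 = 30.4 days, for a visit at month 4.

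**Share of the uncovered changes that would precede the sample**

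Let the visit be at month 3 + *t*, with 0 ≤ *t* ≤ 1, and assume planned dates are spread evenly over month 3 to 4. The share falling before the sample is then *t*.

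| Visit at month | *t* | Share before sample |
|---|---|---|
| 3 | 0 | 0% |
| 3.5 | 0.5 | 50% |
| 4 | 1 | 100% |

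If visits are also spread evenly over the window (a second assumption), the average share is the integral of *t* from 0 to 1, which is 0.5. This is a share of an unknown and possibly very small number of changes.

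**What one affected participant could do (illustration only)**

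The protocol gives no drug effect on LDL, so assume 0.5 to 1.5 mmol/L. With 10% attrition, as section 11.2 assumes, about 16 × 0.9 ≈ 14 controls and 48 × 0.9 ≈ 43 participants per active arm remain.

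- One control: 0.5 / 14 = 0.04 to 1.5 / 14 = 0.11 mmol/L shift in the control mean.
- One active-arm participant: 0.5 / 43 = 0.01 to 1.5 / 43 = 0.03 mmol/L shift in that arm's mean.

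The target difference is 0.3 mmol/L. A drug started shortly before the sample would have less than its full effect, so these are upper-end figures for each assumed effect.

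**The protocol's LDL power**

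The 60% is quoted only as context. It does not reproduce from its stated inputs. The standard error is 0.8 × √(1/16 + 1/48) = 0.231, so 0.3 / 0.231 = 1.30, and the two-sided 5% power is Φ(1.30 − 1.96) ≈ 25%. That is a separate matter and nothing here depends on it.

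**The case against.** The strongest reply is that the protocol uses three months as the name of the follow-up period. Section 6 equates it with the time to final follow-up, and the month-4 limit is only a scheduling tolerance on a visit titled as the three-month assessment. If the phrase means the whole period to the final visit, the gap disappears. That reading is reasonable for the request in section 8.5.1, which refers to the three months of follow-up as a named period; the request is therefore ambiguous and is not counted here as a second gap. It does not carry over to section 7.3. There the words set a calendar horizon counted forward from the day the question is asked, and neither a participant nor a GP answering it would have reason to include month 4.

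A second reply is that the request itself would defer any non-urgent change until after the sample. It may well help, and it reduces the expected number of affected samples. But it is a request rather than a rule, it allows necessary changes, and whether it covers month 3 to 4 is unclear.

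A third is that medication changes are recorded, so the analysis can deal with them. Recording identifies the affected participants, and a sensitivity analysis may be in the analysis plan, which was not available for this review. It does not recover the LDL value that would have been seen without the change.

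What stands is that the effect is small, no consequence has been demonstrated numerically, and changes not planned at baseline lie outside this criterion whatever its length.

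**Conclusion.** The mismatch is in the current text. A change planned at baseline for month 3 to 4 does not exclude a participant, and it can precede the final lipid sample by up to about 30 days. The gap follows directly from the two stated windows, given that eligibility and randomisation occur at the same visit. The 50% average share additionally assumes evenly spread visit dates and planned dates.

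The importance is low. No bias is claimed, because plans made before allocation are balanced by randomisation in expectation, and the primary outcome is untouched. The cost is a small amount of avoidable noise in the secondary lipid outcomes, which cannot be sized from the protocol. This is an inexpensive improvement rather than a flaw that threatens the trial's conclusions.

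**What to change.** Make two wording changes.

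1. Section 7.3: exclude people with *planned changes to cholesterol-lowering medication before the follow-up visit (up to 4 months after randomisation)*.
2. Section 8.5.1: make the request not to alter lipid-lowering medication run *until the follow-up blood sample has been taken, unless strictly necessary*. This removes the ambiguity and keeps the clinical exception.

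Sample size, significance level and analysis are unchanged. A few more people may be excluded, and non-urgent medication changes may be deferred by up to one further month. Because the first edit alters an eligibility criterion, it may count as a substantial amendment; section 14.3 requires the Chief Investigator, where necessary, to "obtain approval from the above parties for all substantial amendments to the original approved documents". It could be bundled with another amendment, or adopted in the definitive LDL trial that section 4 envisages.

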# STUDY PROCEDURES

An overview of the study procedures is shown in the study flowchart (Appendix A).

## Screening and Recruitment

Participating practices will be asked to search their electronic health records to screen suitable participants for the study. We will invite practices to participate who have access to a dietary counselling service by a nurse or qualified health professional which can assist with the intervention. As a result of the search, eligible patients will be sent an invitation letter from their GP as part of a staggered mail out. Participants will be provided with contact information and will be encouraged to contact the research team via email if they are interested in taking part and meet all the inclusion criteria.

Prior to the invitation letters being sent, the GP will screen the search list to ensure that all those identified are medically appropriate to participate in the trial. The GP will exclude those that it would be inappropriate to include according to the specified exclusion criteria and those not able to meet the demands of the study or unlikely to adhere to study procedures as stated in the protocol.

## Eligibility Assessment

Participants who are interested in taking part will contact the central research team on the email provided to them in their letter from the GP. The central research team will discuss study participation with potential participants (by telephone) and undertake eligibility assessment. If the potential participant appears eligible and would like to attend a baseline assessment to confirm eligibility, they will be offered an appointment at their GP practice.

The central research team will post a Participant Information Sheet (PIS) and confirmation letter. Participants will be asked to complete the first 24h dietary recall before the first baseline visit. This data will be stored independently of the study team before full consent is obtained. Participants will be also informed that any data provided before the baseline visit will be destroyed if they decide not to continue taking part in the study, are found to be ineligible or they don’t attend the baseline visit.

When the participant attends the practice, the central research team will provide information as described in the PIS to seek informed consent and will check eligibility for inclusion in the study by assessing the inclusion and exclusion criteria as described above; and confirming elevated LDL cholesterol with the blood sample taken at this baseline visit.

## Informed Consent

The central research team will explain the demands of the trial and answer potential participants’ questions. It will be clearly stated that the participant is free to withdraw from the study at any time for any reason without prejudice to future care, without affecting their legal rights, and with no obligation to give the reason for withdrawal.

The participant will be allowed as much time as wished to consider the information, and the opportunity to question the Investigator, their GP or other independent parties to decide whether they will participate in the study. Evidence of consent will be obtained in writing by means of participant dated signature and dated signature of the person who presented and obtained the consent. The person who obtained the consent will be suitably qualified and trained in Good Clinical Practice procedures, and have been authorised to do so by the Chief Investigator. A copy of the signed consent form will be given to the participant and a copy will be given to the participant’s GP. A scanned copy will be sent to Tesco. The original signed form will be retained by the central research team.

Since the intervention involves providing participants with a personalised report on their previous shopping at Tesco supermarkets, consent to access the storecard data will be obtained by the central research team. Tesco's team will be given the name and storecard number of the participants in the study in order to arrange data transference between Tesco and the central research team. Consent will be sought from participants to allow this and a copy of the consent form will be given to Tesco. Tesco will not receive any additional information about participants as a result of the study.

## Randomisation, blinding and code-breaking

Once the blood test taken during the first baseline visit confirms that the participant has raised LDL cholesterol (>3 mmol/L) and after confirming that they have completed a second 24h dietary recall (details in the next section), and provided their Tesco’s storecard details, the central research team will randomise all eligible participants (until we reach our target sample size) with an allocation ratio of 1:3:3 to control or one of the two active interventions using the online RedCap program which ensures full allocation concealment as information on future allocations are not accessible to the person randomising. Allocation will use block randomisation with randomly varying block sizes of size 7. Once randomised, participants will be booked for a second baseline visit in which they will receive their intervention depending on the group they have been allocated to.

Due to the nature of this trial, it will not be possible to blind participants, clinicians or some of the central research team to the treatment allocation. Nevertheless, the primary outcome will be a measure of saturated fat intake collected through a web-based questionnaire which individuals will fill in individually without any involvement from the study team. The brief advice intervention will be delivered by the practice nurse, who won’t be aware of the treatment allocation within the active intervention arms.

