# APPENDIX C: AMENDMENT HISTORY

| **Amendment No.** | **Protocol Version No.** | **Date issued** | **Author(s) of changes** | **Details of Changes made** |
| --- | --- | --- | --- | --- |
| 1 | 2.0 | 1^st^ October 2017 | [name] | - Added details of data sharing with Tesco to the introduction.  - Changed to fingerprick blood analyses, samples taken by study team.  - Added a new secondary outcome: intake of high SFA foods as it is important to know changes in those in addition to changes in total SFA intake  - Changed slightly the study procedures to clarify that interested participants should contact the study team via email and to explain that we will ask participants to provide a dietary recall before the baseline visit. These changes to the procedures will improve efficiency of the study.  - Changes/clarifications to inclusion/exclusion criteria. One new exclusion criterion is those who started medication in the last 3 months.  - Added clarification about study consent with regards to Tesco’s information  - Only changes to intervention acceptability will be collected so no changes in demographics, health behaviours or shopping habits will be collected at follow up as baseline information is sufficient.  - Added a paragraph about collecting till receipts as a contingency plan in case the collaborating supermarket is unable to provide the data needed to generate the feedback report.  - Paper CRFs will only be needed when computer/internet not working  - Deleted some information from the purchasing report which won’t be provided (total kcal)  - Clarify that SAEs for this study will be considered unexpected  - Added details of how the dietary data is collected and stored |
| 2 | 3.0 | 1^st^ February 2018 | [name] | - Added additional funding source  - Few clarifications/typos throughout  - Clarification in inclusion criteria that participants need to have a registered clubcard exclusively registered under their name  - Clarification to exclusion criteria so that people recently involved in other studies will not be eligible if the nature of the intervention in which they participated will likely affect the outcomes of this study.  - Use of RedCap for CRF data collection  - Randomisation will not be stratified by GP and block size will be 7, as suggested by the statistician to avoid problems with block sizes.  - More information about our primary analysis as it wasn’t clear in the previous paragraph. |

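### Block sizes are called randomly varying but the only size given is 7, so about 45% of control-versus-active assignments are deducible by a recruiter who knows the size and tracks the list

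*Protocol*

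**What the plan says.** Protocol section 8.3 (Randomisation, blinding and code-breaking) sets the scheme: "Allocation will use block randomisation with randomly varying block sizes of size 7", "with an allocation ratio of 1:3:3 to control or one of the two active interventions". It relies on an online system "which ensures full allocation concealment as information on future allocations are not accessible to the person randomising". Section 11.2 gives the totals: "16 participants will be allocated to control, and 48 participants will be allocated to each of the two active interventions". The amendment history records for version 3.0 that "Randomisation will not be stratified by GP and block size will be 7", on the statistician's suggestion, to avoid problems with block sizes. It agrees with the current text and is used here only as corroboration.

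On who does what, section 8.3 says "the central research team will randomise all eligible participants", and the Eligibility Assessment section says "The central research team will discuss study participation with potential participants (by telephone) and undertake eligibility assessment". The same team takes consent and makes the baseline measurements. Sections 6 and 8.3 say that part of this team cannot be blinded to allocation, section 6 adds that those concerned are blind at the moment of randomisation, and section 13.3 calls the trial open label.

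**The concern.** The sentence on blocks cannot be implemented as written. It promises random variation in block size and then names a single size. Read literally, with 7 as the only size, it describes fixed blocks with one control each.

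Fixed, known blocks in an open-label trial weaken concealment even when the list is hidden. Once the block's control has been assigned, everyone else in that block must be active. If the first six are active, the seventh must be control. A member of the team who sees past assignments can work this out before the next participant is screened or booked. Some eligibility items leave room for judgement (wanting dietary support, shopping mainly at one chain, being the main household shopper), so foreknowledge could influence who enters which arm. The primary outcome is self-reported diet, and the planned control arm has 16 people, so two wrongly influenced entries would be 2/16 = 12.5% of the comparator for both intervention-versus-control tests.

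**Working it through.** **Inputs.** Block size 7 and ratio 1:3:3 (section 8.3); 16/48/48, total 112 (section 11.2); one list not stratified by practice (amendment history).

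**The plan's own figures.** 112/7 = 16 complete blocks; 112 × 1/7 = 16 controls; 112 × 3/7 = 48 per active arm. The totals fit blocks of 7 exactly. The protocol gives no figure for predictability.

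**Control versus active, fixed blocks of 7.** The control is equally likely to be in position 1 to 7. If it is in position k, the 7 − k later slots are certainly active. If it is in position 7, that slot is certainly control.

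- Certainly active per block: (6+5+4+3+2+1+0)/7 = 21/7 = 3, and 3/7 = 42.9% of allocations.
- Certainly control per block: 1/7, and (1/7)/7 = 1/49 = 2.0% of allocations.
- Total: 22/7 of 7 slots = 22/49 = 44.9%. Over 16 blocks, 16 × 22/7 = 50.3 of 112 participants, of whom 16 × 1/7 = 2.3 are certain controls.

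By position 1 to 7, the chance that status is certain is 0, 14, 29, 43, 57, 71 and 100%. Enumerating all 140 orderings of a block gives the same total.

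**Exact arm.** The arm is certain when all remaining slots belong to one arm, so the expected number of such slots is the expected length of the final run in the block: 1 + 2 × (3/7 × 2/6) + 2 × (3/7 × 2/6 × 1/5) = 1 + 10/35 + 2/35 = 47/35. Divided by 7, this is 19.2%.

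**Gain over simple guessing.** With no knowledge of the blocks, always guessing active is right 6/7 = 42/49 = 85.7% of the time. The tracker gains only at a last slot known to be control, 1/49 of allocations, and so is right 43/49 = 87.8% of the time. While no control has appeared, however, its probability rises through the block: 1/7, 1/6, 1/5, 1/4, 1/3, 1/2, 1.

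**Blocks of 7 and 14 in random order.** The two sizes and their equal probability are assumptions, since the protocol names only 7. Simulating 112 allocations, with an observer who knows the possible sizes and tracks everything, gives about 11% certain as control versus active (runs gave 11.2 to 11.6%). Fixed blocks of 14 would still give about 29%, so the gain comes mainly from the variation.

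**The case against.** Several points on the other side are sound.

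- **Most of the 44.9% adds little to the ratio.** 42.9 points are certainty of active, which was already 85.7% likely. Certain control is 2.0%, about two people. The overall success of guessing rises by only about two points.
- **The comparison of the two active arms is less exposed.** Knowing that the next person is active does not say which active arm, and the exact arm is certain for only 19.2%.
- **The steering route is narrow.** GPs screen the lists and patients make first contact. Randomisation follows consent, a measured LDL above 3 mmol/L, two recalls and storecard details. Other people may be randomised between a telephone screen and that person's own slot.
- **The primary outcome is protected in part.** It is self-completed online without team involvement and adjusted for baseline. This protects measurement more than it protects who enters which arm.
- **Size 7 was chosen deliberately,** as the amendment history shows. That explains the number but does not answer the predictability.

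Two stronger readings are tempting. A reader might infer that 45% of assignments are simply known to the team. The protocol does not support that: only part of the team is said to be unblinded, and nothing says that one person recruits, knows the block size and follows every assignment. A reader might also infer that the concealment statement is false. It gives as its reason that future assignments cannot be accessed, and nothing in the protocol contradicts that about the list. The fair criticism is that hiding the list does not stop deduction from past assignments.

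**Conclusion.** The contradiction within section 8.3 is plain and does not depend on the amendment history. Read as fixed blocks of 7, the scheme leaves control-versus-active status deducible for 44.9% of allocations, and the exact arm for 19.2%. These are figures for an observer who knows the printed size, sees every earlier assignment on the single list, and also recruits. The protocol neither states that such a person exists nor separates recruiting from randomising staff so as to rule it out.

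The statements on full concealment and on blindness at randomisation therefore claim more than the design delivers. Nothing in the protocol shows that selection took place, and its size cannot be estimated from the protocol. This is a correction that should be made; it does not by itself invalidate the comparison.

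**What to change.** The remedy depends on the stage of randomisation. The qualitative sub-study section, added with version 4.0, counts forty-five potentially eligible people in the intervention 2 arm against 48 planned. Randomisation may therefore be complete or nearly so, although the protocol does not say.

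**If randomisation is still open:** replace the sentence with permuted blocks of 7 and 14 in random order at 1:3:3, load a new table for participants not yet randomised, and keep the sizes in a restricted document away from recruiting staff. The cost is one amended sentence, one new table and a possible imbalance if recruitment stops mid-block, usually of one or two participants. The control arm cannot be off by more than 12/7 = 1.7. In the most extreme ordering of a block of 14 an active arm could be off by 6 − 6 × 3/7 = 3.4.

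**If randomisation is complete:** correct the sentence to the scheme actually used, limit the claim to concealment of the list, qualify the statement about blindness at randomisation in section 6, and report the predictability as a limitation, with the 44.9% (42.9% active, 2.0% control) and 19.2% figures and their conditions if blocks of 7 were used. This costs only text.
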